### Exclusion criteria

(1) Unable to walk independently before onset(2) Cognitive dysfunction before onset(3) Previous neuromuscular disorders (e.g., severe muscular atrophy, amyotrophic lateral sclerosis, myasthenia gravis, etc.)(4) Severe fractures, spinal cord injury, deep vein thrombosis, etc., need to be stopped(5) The onset time was ≥ 7 days, and the treatment was completed in the ICU of another hospital(6) Pregnancy(7) When the patient has a pacemaker(8) Death within 24 h(9) End-stage malignant tumor(10) The patient or his authorized client refused to participate in this study

### Participant recruitment

Patients meeting the eligibility criteria will be screened from the Department of Critical Care Medicine, the Second Affiliated Hospital of Chongqing Medical University. The recruitment period will be April 2023–April 2025. To screen SAP patients with ARDS, a physician in critical care medicine will complete the clinical diagnosis within 48 h of the patient’s admission and then will refer them to a physical therapist to assess whether the patient would be eligible to participate in this trial. Eligible patients will be randomly divided into the NEMS group or control group by an investigator. Baseline assessment will be completed after signing the informed consent form. Considering the risk of muscle wasting in the early stage of bed rest, patients will be given corresponding intervention immediately after participating in the trial. Investigators will check the list of eligible patients daily to determine whether the patients completed the assessment and intervention of the trial process. In addition, investigators will be responsible for maintaining long-term contact with patients and communicating about patient recovery, improving patient adherence, and reducing the failure rate of follow-up.

### Randomization

Numbers 1 to 80 will be randomly divided into the NMES group and control group using the SPSS 26.0 (IBM, USA) software by two investigators who were not involved in the trial. Another two investigators will make envelopes to hide groupings. The number can be seen on the surface of the envelope, but group information is inside the envelope. To ensure that the trial is blind, only investigators will have the authority to access envelope information. Eligible patients will be numbered in the order of the time they participated in the trial, and the investigators will open the envelope according to the patient number to determine the grouping of patients and further arrange for the patient to receive corresponding trial interventions.

### Blinding

This study was designed as a single-blind trial. Patient grouping, intervention, and assessment will be arranged by two investigators who are aware of the grouping. Assessors and statisticians will be blinded to the patient grouping. Because NEMS is electrical stimulation physical therapy, patients cannot be blinded. Unless an adverse event occurs, the blindness will not be broken until the end of the study.

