### Safety assessment and monitoring

NMES intervention will be carried out strictly based on the instrument operation specifications and implemented by two physiotherapists who have completed operation training. Patients will be informed of the potential adverse events of NMES and sign an informed consent form. Adverse events may occur during treatment: mean arterial blood pressure < 65 mmHg, 40 bpm < heart rate < 130 bpm, SpO_2_ < 88%, skin redness, skin burns, skin blisters, pain, myocardial ischemia, and arrhythmia. The NMES group will complete NMES therapy under the supervision of a physiotherapist. During treatment, any patient discomfort will be dealt with immediately (reduce the intensity of electrical stimulation or stop the intervention). The research team will judge the severity of adverse events and analyze the correlation with the intervention. Patients who suffer harm or complications caused by the intervention will receive medical treatment at the Second Affiliated Hospital of Chongqing Medical University free of charge. All serious adverse events will be reported to the ethics committee within 48 h.

Based on the sequential study design, the primary outcome will be analyzed when 50% of participants (40 participants) have randomly enrolled to complete the intervention and data collection. An independent statistician who is blinded to the intervention process will be responsible for performing the data analysis. Type I error statistical analysis will be performed using the Pocock approach with *α* = 0.05. The interim analysis results will be reported to the data monitoring committee (DMC). The DMC will access all data and discuss to decide whether the trial should be continued, modified, or halted earlier than intended.

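### The blinding rule lets any adverse event, with no limit by seriousness or need to know, open the evaluator blind, and such unblinding could fall more on the NMES arm before the MRC score is rated

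*Protocol article*

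**What the plan says.** The protocol article describes a single-blind trial in which the evaluator is the blinded party (Study design). Its Blinding section sets out who knows what:

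- Blinded: "Assessors and statisticians will be blinded to the patient grouping".
- Not blinded, patients: "Because NEMS is electrical stimulation physical therapy, patients cannot be blinded".
- Not blinded, organisers: "Patient grouping, intervention, and assessment will be arranged by two investigators who are aware of the grouping".
- The exception: "Unless an adverse event occurs, the blindness will not be broken until the end of the study".

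Safety assessment and monitoring presents the adverse events as potential effects of the stimulation ("Patients will be informed of the potential adverse events of NMES and sign an informed consent form") arising while it is given. The list starts with vital signs ("Adverse events may occur during treatment: mean arterial blood pressure < 65 mmHg, 40 bpm < heart rate < 130 bpm", then low oxygen saturation) and ends with "skin redness, skin burns, skin blisters, pain, myocardial ischemia, and arrhythmia". Supervision of sessions is described for one arm: "The NMES group will complete NMES therapy under the supervision of a physiotherapist". Discomfort is handled by turning the stimulation down or stopping it.

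Controls receive no NMES (Control group intervention), and no sham procedure is described for them. The primary outcome is the MRC score, a 0 to 5 grade per muscle group with a total of 60, rated at baseline and at 7 days postintervention.

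**The concern.** Evaluator blinding is the only blinding in this trial. The primary outcome is a rater's grade of the patient's maximum contraction, and the patient already knows the allocation. An uninformed rater is therefore the main remaining protection against biased scoring.

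As written, the exception lets that protection lapse for something as slight as reddened skin under an electrode. If unblinding follows such events, it would occur more often among NMES patients, and before the post-treatment rating. An assessor who learns the allocation of an NMES patient may score more favourably, and nothing in the control arm would balance this. Grip strength, limb circumference and the Barthel Index are also collected by evaluators and would be exposed in the same way.

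**Working it through.** The plan gives no figure on this point, so the main check is to read the sections together.

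**Step 1. Whose blind can be broken?** Patients know their group. So do the two arranging investigators. The two physiotherapists who give NMES (Intervention) necessarily know it too. That leaves assessors and statisticians, so the exception can act only on them.

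**Step 2. Is the exception narrowed elsewhere?** Safety assessment and monitoring does not mention unblinding. Ethics and dissemination refers to unblinding as a circumstance in which access to patient information changes, but names no threshold and no procedure. The exception therefore stands unqualified.

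**Step 3. Does handling an adverse event require it?** The stated response is to reduce or stop the stimulation, under a physiotherapist who already knows the allocation. The document states no need for a blinded assessor to be told.

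**Step 4. Which listed events are tied to one arm?** There are nine items.

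| Items | Can they occur in controls? |
|---|---|
| Skin redness, burns, blisters (3) | Not at electrode sites; controls have no electrodes |
| Pain (1) | Stimulation pain no; pain from the disease yes (abdominal pain is a diagnostic item under Inclusion criteria) |
| Blood pressure, heart rate, oxygen saturation, myocardial ischemia, arrhythmia (5) | Yes |

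The asymmetry is firm for the three skin items and for stimulation pain, and not for the other five. As printed, the heart-rate item covers the range between its two limits. Read literally this widens the trigger further, and the item needs reconciling.

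**Step 5. Order in time.** The sessions run over 7 days and the MRC score is rated after them, so an unblinding during treatment would precede the primary rating.

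**Step 6. Illustration of size (all inputs assumed except n).** Let r be the share of NMES patients with an event, u the share of those events that lead to unblinding of the assessor who scores the outcome, and b the tilt in that assessor's scoring, in SD units. Control ratings are taken as unaffected.

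- Share of the NMES arm rated unblinded: q = r × u.
- Bias in the group difference: q × b.
- With n per arm, the test statistic shifts by m = q·b / √(2/n).
- Two-sided error with no true effect: 1 − Φ(1.96 − m) + Φ(−1.96 − m).

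With n = 40 per arm (half of the planned 80), √(2/40) = 0.2236:

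| q | b (SD) | q × b | m | Actual error |
|---|---|---|---|---|
| 0 | any | 0 | 0 | 5.0% |
| 0.25 | 0.2 | 0.05 | 0.224 | 5.6% |
| 0.25 | 0.5 | 0.125 | 0.559 | 8.7% |
| 0.50 | 0.2 | 0.10 | 0.447 | 7.3% |
| 0.50 | 0.5 | 0.25 | 1.118 | 20.1% |

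In points, an assumed tilt of 2 MRC points with q = 0.30 to 0.50 shifts the difference by 0.30 × 2 = 0.6 to 0.50 × 2 = 1.0 on the 60-point scale. The documents give no value for r, u or b, and u could be near zero.

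**The case against.** **The sentence permits; it does not order.** A reader might infer that every adverse event must lead to unblinding, so that assessors would routinely learn who had NMES. The text does not say this, nor does it say who would be told. The link from skin redness to an unblinded assessor comes from joining two sections, one of which never mentions unblinding. This stands, and the point is therefore put as what could happen.

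**The events are not confined to one arm.** A reader might also infer that the trigger falls almost wholly on NMES patients. Five of the nine items can occur in controls with organ failure and ARDS, and pain is only partly specific. No section restricts monitoring to NMES sessions, and the data monitoring committee watches adverse reactions throughout the study. This also stands.

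**A condensed article leaves procedure to the full protocol.** That covers an unblinding procedure that is not printed. It does not cover a rule that is printed and is too wide as stated.

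**There may be a use for the allocation.** The research team judges how an event relates to the intervention, and Study design has a physician and a therapist performing both assessment and treatment, so roles may overlap. But people who already know the group can judge causality. If roles do overlap, that is a further reason to state that outcome assessors stay blinded.

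**Patient effort is open to bias anyway.** This is true, and the change below does not remove it. It protects the rater's share of the bias only.

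**Conclusion.** The point holds in a limited form. The adverse-event exception is unqualified and can act only on the trial's sole blinded parties. It has no stated safety purpose, and it could unblind assessors more often in the NMES arm before the primary rating. This rests on the text alone: who is blinded, what is listed, the absence of electrodes in controls, and the timing of the MRC score.

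The documents do not support a claim that assessors will be unblinded selectively, or any stated amount of bias. The illustrative error rates run from 5% (no scoring assessor unblinded) to 20.1% (half the NMES arm rated unblinded with a 0.5 SD tilt), and both the shares and the tilt are assumptions. It is a cheap improvement to a badly fixed rule and does not show that the primary comparison is invalid.

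**What to change.** Replace the last sentence of the Blinding section with:

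> Outcome assessors and statisticians remain blinded until database lock regardless of adverse events, which are handled by staff who already know the allocation. Any accidental unblinding of an assessor is recorded with date, reason and arm, and where the other of the two planned evaluators is still blinded, that evaluator completes the patient's remaining assessments.

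The two evaluators are already planned under Data collection and statistical analysis. The cost is one sentence, a little logging and an occasional reassignment between them. Handling of adverse events is unchanged, because it already lies with staff who know the allocation. Separately, the printed heart-rate item in the adverse-event list should be reconciled with its intended meaning.

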### Intervention

Two physiotherapists with more than 5 years of clinical experience from the Second Affiliated Hospital of Chongqing Medical University will be responsible for the trial’s intervention. After undergoing standardized operation training, two qualified physiotherapists will administer NMES therapy to the NMES group. Meanwhile, the control group will receive standard usual care only. The intervention will last 7 days.

#### NMES group intervention

NMES intervention will be performed on the first day of patient enrollment, and the intervention will continue for 7 days (Fig. 2). During the intervention, patients will take a supine position with the head elevated 30°, and the position of both lower limbs will be 15° hip flexion and 30° knee flexion to achieve the best muscle contraction [28]. Four groups of self-adhesive electrodes (5 cm × 5 cm) will be placed on motor points (rectus femoris, anterior tibial). The NMES intervention will be designed 60 min/day, including a 5-min warm-up, 50-min stimulation sessions, and a 5-min cooldown. The stimulation frequency of warm-up is 4 Hz, and the intensity will gradually increase to achieve visible contractions. Fifty-minute stimulation sessions consisted of 10 s of contraction stimulation (pulse width = 300 μs, frequency = 45 Hz), and the stimulation intensity met maximum muscle contraction without causing discomfort. In addition, a 5-s rest phase with a 4-Hz stimulation frequency will be performed. Cooldown sessions (frequency = 45 Hz) are composed of gradually decreasing intensity. During whole intervention sessions, intensity will be increased to avoid tissue accommodation. The physiotherapist will monitor the intervention period to prevent adverse reactions. In addition, NMES participants will receive routine care during the 7-day NMES intervention.

**Fig. 2 Fig2:**
[figure not shown]
Intervention process of NMES for severe acute pancreatitis complicated patients with acute respiratory distress syndrome

### Control group intervention

The control group will not receive NMES treatment. Routine care for the control group guided by treating clinicians, including health education, suction, regular turnover per 2 h, and elevating the head of the bed, will be completed by nurses. Early physiotherapy will be provided by physiotherapists. Patients who are unable to cooperate with sedation therapy will receive passive range-of-motion exercises. Responsive patients will be encouraged to receive out-of-bed mobilization and active exercise therapy (strength training, balance, standing, and walking). Early physiotherapy will be delivered according to physiotherapy intervention recommendations [29].

### Outcomes

#### Baseline characteristics

Participants’ baseline characteristics will be evaluated on the first day of enrollment. The following values will be recorded before the intervention: age, sex, duration of symptoms, respiratory rate, oxygen saturation, blood pressure, oxygenation ratio, abdominal circumference, intra-abdominal pressure, hemodialysis intervention, Marshall score, and APACHE II score. The baseline characteristics are shown in Table 2.

**Table 2 Tab2:**
[figure not shown]
Patient’s characteristics

#### Primary outcome

##### MRC score

MRC score clinical assessments will be performed at baseline, and 7 days postintervention, MRC has proven to be a valid and reliable assessment scale to evaluate muscle weakness in critically ill individuals [30, 31]. MRC, as a convenient muscle strength assessment tool, is graded according to maximum muscle contraction, ranging from 0 to 5. The grade details are as follows: 0 = no contraction, 1 = visible and/or palpable contraction without limb movement, 2 = active movement, with gravity eliminated, 3 = active movement against gravity, 4 = active movement against gravity and submaximal resistance, and 5 = active movement against gravity and maximal resistance [32]. The MRC score was obtained by evaluating 6 groups of bilateral muscles. These include wrist dorsiflexors, elbow flexors, shoulder abductors, hip flexors, knee extensors, and ankle dorsiflexors. The total MRC score is 60, and higher MRC scores indicate better muscle strength [31].

#### Secondary outcomes

##### Grip strength measurements

Grip strength assessment will be performed at baseline and 7 days postintervention. Grip strength is a cost-effective clinical tool for muscle strength assessment. It is a strong predictor of sarcopenia. Additionally, lower weakness grip strength is associated with a higher risk of mortality [33]. Evaluators will use a CAMRY electronic hand dynamometer (EH101 Instruments, Guangdong, China) for grip strength assessment. In the bedside sitting position, participants will be asked to squeeze the dynamometer as hard as possible. The grip strength of each hand will be tested two times, and grip strength will be calculated through the average of the maximum values of the patients’ bilateral hands.

##### Lower limb circumference measurements

Lower limb circumference measurement assessments will be performed at baseline and 7 days postintervention. Trained evaluators will assess limb volume and appendicular skeletal muscle by measuring the patient’s lower limb circumference [34, 35]. The patient’s thigh and calf circumference dates will be measured with inelastic tape. Due to mobility limitations, patients will complete the circumference measurement in the supine position with hip and knee flexion. The thigh circumference will be measured midway between the inguinal fold and the base of the patella. Calf circumference will be measured at the maximum circumference between the knee and ankle. Both thigh and calf circumferences will be analyzed by adopting the mean of the left and right legs from the average of the two measurements for each leg.

##### Diaphragm ultrasound

Diaphragm ultrasound assessments will be performed daily. The diaphragm thickness and thickening fraction will be measured by ultrasound (LOGIQ Book, GE Healthcare, Waukesha, Wisconsin, USA). For patients in supine positions, diaphragm assessment will be performed using M-ultrasound with a 6–12 MHz frequency ultrasound probe at the 8th to 10th intercostal space of the right midaxillary line. The distance between the pleura line and peritoneum line will be measured as the thickness of the diaphragm (tdi) at the end-expiration. The thickness of the diaphragm will be obtained by averaging the measurements over three breathing cycles. In addition, the thickening fraction will be calculated as ((tdi end-inspiration − tdi end-expiration)/tdi end-expiration) × 100%. A low-frequency convex transducer is placed below the costal margin of the midclavicular line and anterior axillary line. Then, diaphragmatic excursion of the right hemidiaphragm will be recorded during quiet breathing.

##### APACHE II score

The APACHE II score assessment will be performed at baseline and 7 days postintervention. The APACHE II score is a severity-of-disease classification system for critically ill patients, with a total score ranging from 0 to 71 points. Higher scores correspond to a worse prognosis. The APACHE II score consists of the acute physiology score, age points, and chronic health points. The physiological variables of the Acute Physiology Score include body temperature, mean arterial pressure, heart rate, respiratory rate, A-a PO_2_ or PaO_2_ (for FiO_2_ ≥ 0.5 or < 0.5, respectively), blood pH or HCO_3_, serum sodium, serum potassium, creatinine, hematocrit, white blood cell count, and GCS. Acute Physiology Score was measured by nurses starting within 24 h of admission.

##### Modified Marshall score

Modified Marshall score assessment will be performed at baseline and 7 days postintervention. The modified Marshall score is an efficient classification tool for acute pancreatitis organ failure. The scale will rate respiratory status (PaO_2_ to FiO_2_), renal status, and cardiovascular status (systolic blood pressure, mmHg) on a scale of 0 to 4, with a score of 2 or above in any organ system indicating organ failure.

##### SOFA score

SOFA score assessment will be performed at baseline and 7 days postintervention. The SOFA score is traditionally employed in determining acute morbidity or the efficacy of clinical interventions in critically ill patients. The tool involves six criteria of respiratory, cardiovascular, hepatic, coagulation, renal, and neurological systems, in which each organ is scored on a scale of 0–4; the worse the organ dysfunction/failure, the higher the score.

##### Barthel Index

Barthel Index assessment will be performed at baseline and 7 days postintervention, and Barthel Index follow-up data will be collected in the 1st month, 3rd month, and 6th month after discharge. The Barthel index is used to assess the recovery of daily life function in critically ill patients, and it values ten items (personal hygiene, bathing self, feeding, toilet, stair climbing, dressing, bowel control, bladder control, ambulation, chair/bed transfers), yielding a score of 0–100. A higher score is associated with a greater degree of independence in daily life.

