## Introduction

Acute pancreatitis (AP) is a common disease in clinical practice due to an inflammatory disorder of the pancreas [1]. Twenty percent of AP patients may develop systemic inflammation leading to organ failure, defined as “severe acute pancreatitis (SAP)” [2–4]. Previous studies have demonstrated that the lung is the commonly damaged target organ caused by early induction of systemic inflammatory response syndrome (SIRS) in SAP [5]. One third of patients with severe pancreatitis develop acute lung injury (ALI) and ARDS in the first week [6], and these complications are responsible for high mortality and ICU admission [7–9]. In addition, blood purification, respiratory support, and sedation are common treatments but cause long-term bed rest for SAP patients with ARDS. Patients who stay in bed can experience muscle atrophy in the early stage. Studies have shown that the rectus femoris cross-sectional area decreases rapidly during the first week of bed rest; furthermore, muscle atrophy is more pronounced in patients with multiorgan failure [10, 11]. Muscle wasting is associated with reduced muscle strength and exercise capacity. The decline in exercise capacity is related to poor quality of life, increased mortality, and financial burden on healthcare [12–14]. Early intervention to reduce muscle wasting during the first week of bed rest in patients with SAP complicated with ARDS is urgently needed.

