Several protocols have been proven to be feasible interventions to prevent muscle wasting in ICU patients. However, early mobilization and physical exercise are limited due to sedation, dyspnea, increased intra-abdominal pressure, or blood purification for the acute phase of SAP. NMES is an effective and common intervention to prevent muscle atrophy in clinical practice. NMES sends electrical impulses transcutaneously to motor neurons, causing involuntary muscle contractions. Studies have revealed that NMES is a convenient, safe, and beneficial intervention for early immobilization in the ICU [15, 16]. In patients who prolonged bed rest and inactivity, some studies have found that NMES can reduce muscle atrophy and preserve muscle strength [17, 18]. Furthermore, NMES can preserve fiber cross-section (CSA) and higher gene expression for myosin heavy chains [19, 20]. However, other studies have found that NMES is not a useful adjunct to revert muscle wasting and muscle layer thickness, especially for acute patients in the ICU [21–23]. In addition, Gutiérrez-Arias et al. revealed that NMES may reduce the duration of invasive mechanical ventilation for ICU patients, but the mechanism of the impact of NMES on ventilator weaning is unclear [24]. At present, there is insufficient evidence indicating that NMES intervention results in clinically important changes in muscle strength, respiratory function, and functional status for SAP patients with ARDS.

This trial aimed to investigate the effectiveness of NMES on function status outcomes in patients with SAP complicated with ARSD and to investigate the effects of NMES on muscle atrophy, diaphragm function, multiple organ dysfunction, and quality of life after discharge.

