## Method

### Study design

The overall objective of this trial is to explore the superior effects of NMES on preventing muscle wasting in patients with early SAP complicated with ARDS compared with sham intervention. We designed a randomized, prospective, single-blind trial (evaluator) because stimulation and contraction evoked during NMES therapy cannot be blinded to patients. Eighty patients who meet the inclusion criteria will be randomly divided into the NMES group and the control group at a ratio of 1:1. All participants will complete data collection and follow-up interviews. Assessment and treatment will be performed by a physician and therapist with 5 years of clinical experience, and diaphragm ultrasound evaluation will be performed by trained sonographers. Participants’ clinical assessments will be performed at baseline and 7 days postintervention, diaphragm ultrasound assessments will be performed daily, and follow-up assessments will be completed at months 1, 3, and 6 after discharge. The NMES group will receive neuromuscular electrical stimulation intervention and usual care for 7 days within 48 h of ICU admission, and the control group will receive the usual care only. The flowchart and study process are shown in Fig. 1 and Table 1, respectively.

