### Data collection and statistical analysis

Two trained evaluators will collect baseline data, outcomes, and follow-up data. Participant trial data will be recorded through the case report form. Participants will be informed of follow-up visits after discharge from the hospital, and follow-up data will be obtained through telephone questionnaires or home visits. Two investigators will check the case report form twice to ensure accuracy and completion and record the data of the case report form into the Excel file with double-check.

All participants can withdraw from the trial at any time. If participants terminate the trial or deviate from the intervention protocol, the investigators will record the trial data from the participant’s last intervention and report the reason for withdrawal.

The SPSS 26.0 software (IBM SPSS, Chicago, IL) was applied to analyze the baseline characteristics and outcomes between the two groups. *x̅* ± s will represent continuous variables that conformed to the normal distribution, and the *t* test will compare the differences between the two groups. The Mann–Whitney *U* test will be applied if continuous variables are not normally distributed. Categorical variables will be expressed as frequency (percentage, %), and the chi-square test will be used to compare the differences between the two groups. Effect estimates will be provided with corresponding 95% confidence intervals, and *P* values ≤ 0.05 will be considered significant. Aiming to preserve the unique benefit of randomization, regardless of whether that participant received the allocated intervention, the principles of intention-to-treat analysis will be used. All randomized participants will be included in the analyses, and data will be analyzed in the group in which the participants were originally randomized. All available data from the NMES group that was originally randomized will be analyzed as an intervention group, including participants from the NMES group who do not complete the NMES intervention or even do not receive NMES intervention. Similarly, all available data from the control group that was originally randomized will be analyzed as the control group, including any who receive the NMES intervention. Multiple imputation (MI) using the mice package in R will be applied to analyze the missing data.

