## Discussion

To the best of our knowledge, this is the first study to focus on functional recovery, aiming to explore the effect of early NMES intervention on SAP with ARDS. The changes in muscle mass, diaphragm function, multiple organ dysfunction, and quality of life will be demonstrated after receiving 7 days of NMES intervention. In addition, the effect of early NMES intervention in the 1st month, 3rd month, and 6th month after discharge will be determined through follow-up.

ARDS is a common early complication of SAP, occurring 2–7 days after pancreatic inflammation. Furthermore, Fei et al. [36] indicated that ARDS increases the mortality rate of SAP in the first week of the disease. To ensure the stability of patients’ lives, critical care treatment is needed. Mechanical ventilation, blood purification, sedation, and analgesia are the supportive care for SAP with ARDS. However, critical care treatment impairs the patient’s physical activity, causing physical function to drop sharply in the early stage. A study of patient quality of life showed that survivors of SAP had significantly reduced SF-36 scores compared with age-matched controls, especially in the domains of social and physical function and general health [37]. Although there is currently insufficient evidence that SAP with ARDS will impair muscle mass, SAP and ARDS are major factors that attenuate muscle mass and reduce quality of life, respectively. Several studies have indicated that severe pancreatitis demonstrates a strong association with myosteatosis and muscle attenuation, which is related to poor survival [38, 39]. Dinglas et al. [40] showed that more than 1/3 of ARDS survivors experienced muscle weakness at hospital discharge, and 5-year follow-up outcomes after ARDS onset showed that patients with lower MRC sum scores were associated with higher mortality. The results of the 6-min walk test (6MWD) and SF-36 measures demonstrate that ARDS patients have reduced exercise capacity and quality of life in the first year [41]. To investigate the protocol for preventing physical function impairment, this trial aims to provide sufficient evidence about the efficacy of early NMES treatment in patients with SAP complicated with ARDS.

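### The 1-, 3- and 6-month Barthel visits are timed from hospital discharge, which NMES might alter, so the sustained-effect comparison need not be on a common clock from randomisation

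*Protocol article*

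**What the plan says.** The anchor is the same throughout the protocol article. The Barthel Index section says "Barthel Index follow-up data will be collected in the 1st month, 3rd month, and 6th month after discharge". Study design says "follow-up assessments will be completed at months 1, 3, and 6 after discharge", and the Abstract gives the same schedule. Data collection and statistical analysis shows which discharge is meant: "Participants will be informed of follow-up visits after discharge from the hospital". No section times these visits from randomisation or enrolment.

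The Discussion states their purpose: "the effect of early NMES intervention in the 1st month, 3rd month, and 6th month after discharge will be determined through follow-up". It adds that follow-up is meant to establish whether the NMES effect is sustained. Barthel is the only outcome that the text schedules after discharge.

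On analysis, Data collection and statistical analysis plans a t test or Mann–Whitney test between the two groups. It also says "All randomized participants will be included in the analyses" and "Multiple imputation (MI) using the mice package in R will be applied to analyze the missing data".

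**The concern.** A causal comparison of function at a later time needs both arms measured at the same distance from randomisation. Here the clock starts at discharge, an event that follows treatment. The Introduction reports that "NMES may reduce the duration of invasive mechanical ventilation for ICU patients", so the protocol itself offers a route by which NMES might change when patients go home.

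If it does, a visit labelled month 1 falls at a different point of recovery in each arm, and the two-group test mixes the treatment effect with the difference in stay.

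There is a second consequence. A patient who dies in hospital has no discharge and so no date from which to count, although every randomised patient is to be analysed. The Introduction says of ALI and ARDS in this disease that "these complications are responsible for high mortality and ICU admission", so such patients should be expected.

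What is at stake is the statement about sustained benefit, which rests on these three time points.

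**Working it through.** **What can be checked.** The documents give no length of stay, no in-hospital mortality rate and no Barthel recovery rate, so there is no planned figure to reproduce. The only document figure used below is the 80 patients to be randomised. Everything else is an assumption, used to show the order of magnitude.

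**Step 1. Time since randomisation at a visit.** Let L be the control stay after randomisation in days, g the number of days by which the NMES stay is shorter, and m the visit time after discharge. Control patients are seen at L + m and NMES patients at L − g + m. The gap is g at every visit and zero if g = 0.

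**Step 2. What the gap does to the score.** Assume that both arms follow one recovery curve from randomisation, so that there is no true effect:

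f(t) = 100 − 80·exp(−t/τ), with τ from 60 to 90 days and L from 21 to 28 days.

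The apparent difference, control minus NMES, is

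D(m) = f(L + m) − f(L − g + m) = 80·exp(−(L + m)/τ)·(exp(g/τ) − 1).

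Example with τ = 60, L = 21, g = 7 and m = 30:
- control at day 51: 100 − 80·exp(−51/60) = 65.8
- NMES at day 44: 100 − 80·exp(−44/60) = 61.6
- difference: 4.2 points in favour of control, with no true effect.

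Range over the assumed τ and L, in Barthel points in favour of control:

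| NMES stay shorter by | Month 1 (m = 30) | Month 3 (m = 91) | Month 6 (m = 182) |
|---|---|---|---|
| 0 days | 0 | 0 | 0 |
| 3 days | 1.4–1.8 | 0.6–0.8 | 0.1–0.3 |
| 7 days | 3.4–4.2 | 1.4–1.9 | 0.3–0.7 |
| 14 days | 7.1–9.0 | 2.9–3.9 | 0.6–1.4 |

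If the NMES stay were longer, g would be negative and the sign would reverse.

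**Step 3. Patients without an index date.** With an assumed in-hospital death rate d, the number who never have a discharge-based visit is 80·d:
- d = 10%: 8 patients
- d = 20%: 16 patients
- d = 30%: 24 patients
- d = 40%: 32 patients

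**Step 4. Can the analysis repair it?** The planned tests, as described, do not adjust for time since randomisation. An analysis plan cannot recover measurements at a common time if the visits were never scheduled that way. For patients who die before discharge, the choice is to restrict the comparison to those discharged alive, which is a subset formed after randomisation, or to impute a Barthel score for someone who has died.

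**The case against.** The best case for the protocol is that the anchor is deliberate and consistent. The Introduction names quality of life after discharge as an aim, and the design, outcome and discussion sections agree with it. How patients function once home is a legitimate question. This stands as far as it goes: nothing here is contradictory or miscalculated. But consistency does not make the comparison unbiased when the same visits are used to claim a sustained treatment effect.

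The evidence that discharge will differ by arm is thin, and that stands too. The Introduction says only that NMES may shorten ventilation in ICU patients generally. It calls the mechanism unclear, cites negative studies of NMES on muscle wasting, and says evidence in this population is insufficient. Ventilation time is also not hospital stay. A reader might infer that the schedule is biased against NMES by a known amount. The documents do not support that: every point shift above rests on assumed curves and stays.

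A reader might also infer that long-stay patients drop out of follow-up. They do not; they are assessed, but later. Only death before discharge removes the index date.

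Finally, a new anchor gives a patient who has died no Barthel score, and the scoring of deaths in a secondary outcome is commonly left to an analysis plan, which is not shown. That is right, so its absence is not held against the protocol. The narrower point is that the chosen anchor leaves these patients without even a visit date.

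**Conclusion.** The point holds as a limited one. The three follow-up visits, the only evidence offered for a sustained effect, are counted from an event after randomisation that treatment might alter. The arms therefore need not be compared at the same time since randomisation.

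The size and direction of any bias cannot be found from the documents. It is zero if stay does not differ. Under the assumed curves it is largest at month 1 (up to 9.0 points for a 14-day difference) and small by month 6 (at most 1.4 points).

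It would be wrong to read this as a threat to the main result. The primary MRC outcome and the Barthel assessment at 7 days do not depend on discharge, and the sample size need not change. Only three time points of one secondary outcome are affected. The change is worth making because it is cheap and because later analysis cannot substitute for it.

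**What to change.** - Time the three Barthel follow-ups from randomisation for every patient in both arms, for example at days 30, 90 and 180 with stated windows. Assess patients still in hospital at the bedside.
- Report time to discharge by arm, and the number of deaths before each visit by arm.
- State that Barthel scores for patients who have died will not be imputed as ordinary missing data.
- If the discharge-based visits are kept, label them descriptive and do not rest the sustained-effect claim on them.

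**Cost.** Safety assessment and monitoring requires protocol changes to be reviewed by the ethics committee and the board, so this is an amendment. Telephone or home contact is already planned, so the work is mainly rescheduling. The drawback is that some early assessments will be made in hospital rather than by telephone or home visit, and that mix could differ by arm if stay does. The setting should be recorded at each assessment.
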